#### Chemoprevention Efficacy Cohort Study

We aim to recruit participants from within Lalaua district, one of the new phase 2 implementation districts. Assuming a 3% breakthrough infection rate, sampling 494 children will provide a 95% CI of 1.7% to 4.9%. Assuming a 99% response rate and 1% loss to follow-up, a sample size of 500 children is considered appropriate. We assume that the drug resistance observed for all drugs (ie, SP+AQ) will be the same across a 300-km radius from the location. Therefore, selecting a single health facility should introduce no selection bias when we consider drug resistance prevalence across the region.

#### Resistance Marker Study

The sample size for the survey was determined using a sample size calculation from a WHO protocol for drug efficacy testing [29], with the intention to estimate changes in prevalence of SP- and AQ-resistance markers with enough precision to provide adequate power to detect changes if they occur. A sample of 300 children per district—150 each at baseline and end line—is expected to result in 90% power to detect a difference at the 5% confidence level in sextuple SP mutants from less than 1% to 2%. In Lalaua, where the chemoprevention efficacy study will be conducted, we determined that a sample of 600 children—300 each at baseline and end line—is needed to obtain a sufficiently accurate specific prevalence measure in the absence of data on malaria parasite ecologies. This will result in a total sample size across both districts of 1500, with 750 children sampled at both baseline and end line.

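### The resistance marker study's stated 90% power for sextuple SP mutants (<1% to 2%) is not delivered by 150 versus 150 children per district under any two-sample test tried

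*Protocol article*

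**What the plan says.** Under Sample Sizes, Resistance Marker Study, the protocol article allots 300 children to each district, split as "150 each at baseline and end line", and says that this should give "90% power to detect a difference at the 5% confidence level in sextuple SP mutants from less than 1% to 2"%. The baseline is given only as a value below 1%. No test, sidedness or design effect is given.

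Lalaua is the exception, with "300 each at baseline and end line". That size is justified by precision, without a power figure. The total is 1500, "with 750 children sampled at both baseline and end line", which fits three districts of 300 plus Lalaua's 600.

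Under Recruitment and Data Collection, Resistance Marker Study, the design is a health facility-based cross-sectional survey before SMC and again after one full round, in four facilities per district. Under Data Analysis, the plan for this component is to ascertain allele prevalence and *Pfplm2* copy number. No significance test is named.

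**The concern.** At a prevalence of 2%, 150 children yield three expected sextuple mutants (150 × 0.02). At a baseline below 1% they yield fewer than 1.5. Counts this small cannot separate two surveys reliably, so 90% power is implausible on sight.

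Change in resistance markers as a result of SMC is a specific objective of the study, and marker prevalence is this component's primary outcome. The Discussion already reads phase 1 as showing no apparent harm to the resistance profile after one annual round. If phase 2 finds no significant rise in a district and the reader believes the power was 90%, the null will look like firm evidence that the stated rise did not occur. On the figures below, a single district would usually miss it under standard two-sided tests.

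**Working it through.** **Inputs.** From the sample-size section: n = 150 per time point per district (300 in Lalaua, 750 over all districts), end-line prevalence p2 = 2%, α = 5%, stated power 90%. The two surveys are independent cross-sections.

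**Assumptions.** The baseline p1 is not fixed, so it is varied from 0 to 1%. Taking exactly 1% is the limit of the stated range. Sidedness is not stated, so both are shown. No clustering and no genotyping failure are assumed, which favours the plan.

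**Step 1: try to reproduce 90% (normal approximation, pooled null variance).** With m = (p1 + p2)/2,

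power = Φ{[(p2 − p1)√n − z√(2m(1 − m))] / √(p1(1 − p1) + p2(1 − p2))}.

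- p1 = 1%: (0.1225 − 1.96 × 0.1719)/0.1718 = −1.25, so power is 11%.
- p1 = 0%: (0.2449 − 1.96 × 0.1407)/0.1400 = −0.22, so power is 41%.

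The 90% is not reproduced at either end of the range.

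**Step 2: other two-sample methods, 150 versus 150, end line 2%.**

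| Method | p1 = 0% | 0.1% | 0.5% | 1% |
|---|---|---|---|---|
| Normal, two-sided | 41% | 36% | 21% | 11% |
| Normal, one-sided | 54% | 49% | 32% | 18% |
| Fisher exact, two-sided | 8% | 7% | 4% | 2% |
| Arcsine, two-sided | 69% | 48% | 23% | 11% |
| Arcsine, one-sided | 79% | 60% | 34% | 18% |

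Fisher power is by full enumeration of both binomials. The arcsine figure at p1 = 0 is Φ(2·arcsin√0.02 × √75 − z) = Φ(2.458 − 1.96) = 69%, or Φ(2.458 − 1.645) = 79% one-sided. An exact one-sided uncorrected chi-square test reaches at most 58%.

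**Step 3: a check on counts.** Suppose the baseline shows 0/150. Two-sided Fisher p is 0.060 for 5/150 at end line and 0.030 for 6/150. Six mutants are needed where three are expected, and the chance of six or more out of 150 at 2% is 8%.

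**Step 4: what 90% power would need (normal, two-sided).** n per time point = {[1.96√(2m(1 − m)) + 1.2816√(p1(1 − p1) + p2(1 − p2))]/(p2 − p1)}².

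- p1 near 0%: 519
- 0.1%: 603
- 0.5%: 1,151
- 1%: 3,103

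That is about 3 to 21 times the 150 planned (519/150 = 3.5; 3,103/150 = 20.7).

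**Step 5: what 150 versus 150 can detect.** Solving the Step 1 formula for p2 at 90% power, two-sided, gives a rise from near 0% to about 6.7%, or from 1% to about 9% (9.2%).

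**Step 6: the larger samples (normal, two-sided).**

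| Sample | p1 = 0% | 0.1% | 0.5% | 1% |
|---|---|---|---|---|
| Lalaua, 300 vs 300 | 69% | 63% | 38% | 17% |
| All districts pooled, 750 vs 750 | 97% | 95% | 74% | 36% |

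For Lalaua, Fisher's test gives 56% down to 9%. The arcsine approximation passes 90% there only in the limiting case of a baseline of exactly 0% (94% two-sided); at 0.1% it is 77%.

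**The case against.** **The range depends on choices the article does not state.** A reader might infer that the true power is 2% to 40%. That range joins Fisher's test at a 1% baseline to a two-sided normal test at 0%. The article fixes neither test nor sidedness and puts the baseline below 1%, so higher figures, up to 79%, cannot be excluded. This stands. What can be said is that every variant tried falls short of 90%.

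**The whole sample is larger.** Pooled over districts, power exceeds 90% if the baseline is about 0.1% or lower. This is true, but the power sentence is tied to the per-district sample, and the article gives no such baseline.

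**The figure may have another origin.** It comes from a cited WHO calculation that is not at hand. The chance of seeing at least one mutant among 150 at 2% is 1 − 0.98^150 = 95%, which is not 90%. A one-sample normal approximation against a fixed, known baseline of 0.05% to 0.1% gives 92% to 89%, but it ignores sampling error in the 150 baseline children and is not the design described. At a fixed 1% baseline it gives 30%. The origin remains conjecture, and neither route supports the sentence as written.

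**The component is not uninformative.** A reader might infer that a finding of no change would say almost nothing about resistance. That goes too far. Sextuple mutants are one rare haplotype among many markers. For a commoner marker, a change from 50% to 68% (an illustration; the article gives no marker baselines) has about 89% power at 150 versus 150. The limitation applies to a one-district null for a small shift in this haplotype.

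**False reassurance is not planned.** Data Analysis names no test for this component, so a misread null is a risk, made plausible by the phase 1 wording, and not something the article commits to. The cRCT's primary outcome is unaffected.

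**Conclusion.** The stated 90% power is wrong as written for the per-district comparison. At 150 versus 150 and 2% at end line, with the baseline anywhere from 0 to 1%, two-sided power is 11% to 41% (normal) or 2% to 8% (Fisher), one-sided normal power is 18% to 54%, and the best case tried is 79%. The conclusion rests on reading the design as two independent samples, as the recruitment section describes it. It does not depend on the exact baseline, the test among those tried, or sidedness. Ignoring facility clustering and genotyping failure favours the plan; the article quantifies neither.

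The effect in question is a rise from below 1% to 2%. A reader might call it a doubling, but the text implies more than that. The documents do not show that the component fails for larger shifts, for commoner markers, or for a pooled comparison from a very low baseline.

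**What to change.** - Withdraw the per-district 90% power claim.
- State the baseline prevalence, test and sidedness assumed, and the change that 150 versus 150 can detect with 90% power: two-sided, from near 0% to about 6.7%, or from 1% to about 9%.
- Report prevalence and change for each district with exact confidence intervals.
- State that a non-significant per-district change in sextuple mutants will not be read as evidence of no selection.
- Optionally, add a pooled, district-stratified comparison as a supporting analysis with its own stated power. It need not replace the district comparisons: it mixes two districts already given SMC in phase 1 with two receiving it for the first time, and at 2% only about 15 end-line mutants are expected (750 × 0.02), too few for reliable clustered standard errors over 16 facilities.

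The cost is wording and a less favourable stated power. Data collection ended in mid-June 2022, so the sample is fixed and no further samples are asked for.

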### Recruitment and Data Collection

#### Cluster Randomized Controlled Trial

In the control arm in both districts, compounds will be randomly sampled by researchers using household lists from selected communities, with one eligible child recruited at random from each household. After caregivers provide consent, children will be recruited and a short baseline questionnaire will be administered to collect individual data on each child and to confirm their eligibility. In the intervention arm, a researcher will follow a pair of community distributors as they administer SMC. In addition to variables such as experiences of fever within the past month among selected children, data on a range of variables relating to the selected child, their caregiver, and their household will be collected as part of the survey. These variables will include the selected children’s age, sex, and use of mosquito nets as well as the caregivers’ and heads-of-household’s level of education, occupational position, literacy level, household size, wealth (using the Simple Poverty Scorecard), primary language, and migration status, among other variables. Data on these variables will be collected in order to include potential confounders in the analysis for the association between the receipt of SP+AQ and clinically significant malaria. Children will be given SP+AQ by community distributors via directly observed therapy; in addition, blood samples will be taken and subsequent hemoglobin concentration measured using a HemoCue system (HemoCue AB). Children recruited into the study presenting at clinics will be identified using unique identification numbers and barcodes, and data on clinic visits, including suspected malaria cases and results of RDTs, will be matched to baseline questionnaire data to build a database for analysis.

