### Study Population

The study population that is eligible to receive SMC includes afebrile children [1] of either gender (ie, children with a fever on the day of SMC administration will be excluded and referred to the health facility for further evaluation), aged 3 to 59 months for any of the SMC cycles, and residing in any of the four districts. Children must be 59 months or younger at the start of the first cycle; if they turn 5 years old during the SMC season, they may continue to receive SMC. If children are 2 months old or younger at the first cycle month, they can begin SMC once they are 3 months old in any cycle. During phase 1, when only Mecubúri and Malema districts were included, population data were retrieved from the National Census 2017, adjusting by an annual growth factor of 3.5% in Nampula Province, as calculated by the National Institute of Statistics. For phase 2, population figures for Mecubúri and Malema were obtained through the administrative coverage data of SMC from phase 1. For the two new districts, Lalaua and Muecate, as it was done for districts in phase 1, population figures were retrieved from the 2017 census data, projected for 2021 and considering a growth rate of 3.5% per year (Table 1). Additionally, health workers involved in SMC implementation; caregivers of children younger than 10 years of age; community leaders and key stakeholders, such as health officials at different levels of the health system; and those involved in SMC implementation will be sampled to provide information with regard to the intervention, according to the different study elements.

**Table 1 table1:** Estimated target population of seasonal malaria chemoprevention (SMC) districts.

District	Population^a^ for each eligible children’s group by age, n		
	3-11 months	12-59 months	All children
Malema	8500	35,800	44,300
Mecubúri	7300	36,000	43,300
Lalaua	3200	13,600	16,800
Muecate	1900	8000	9900
All districts	20,900	93,400	114,300

^a^District populations were determined by the National Institute of Statistics and SMC 2021 coverage data.

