### Sample Sizes

#### Cluster Randomized Controlled Trial

Clusters will be selected for the intervention arm at the community level in two districts. The study will be powered to have an 80% chance of detecting a significant reduction in RDT-confirmed malaria incidence at the 5% confidence level using a chi-square test comparing two independent proportions in a cluster randomized design. We are aiming to detect a significant reduction in malaria incidence from 0.2 to 0.12 clinical episodes per child per high-transmission season, corresponding to the SMC round. The clinical episodes should be of sufficient severity to present to a health facility, and the reduction in episodes should be equivalent to an odds ratio of 0.66, or a minimum effect size of 33%. This is based on the assumption that the efficacy of SP+AQ in Northern Mozambique, where the prevalence of resistance alleles in circulating parasites is high, is half of that found in studies in West African settings. To account for the cluster randomized design, we assumed an intracluster correlation for malaria outcomes within communities of 0.23, based on data from SMC coverage surveys conducted by the Malaria Consortium in 2020 [27] and 2021 [28]. A cluster size of 15 children per community was selected, and children in the intervention and control arms were recruited in a ratio of 1:1.5. This resulted in a total sample size of 2850 eligible children in 190 clusters: 1710 in 114 clusters in the control arm and 1140 in 76 clusters in the intervention arm. A total of 76 communities from a list of all communities will be selected as intervention districts using a simple random method. Then, 114 communities will be selected at random from among those remaining for inclusion in the control arm.

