### Data Analysis

#### Cluster Randomized Controlled Trial

First, the characteristics of the eligible children in the intervention and control arms will be described and tabulated; these analyses will use survey weights obtained using population estimates for each community cluster. Next, a chi-square test will be performed to determine whether there is a significant difference in the proportions of children in each arm experiencing at least one confirmed malaria case during the study period, and exact odds ratios will be calculated.

Random-effects Cox proportional hazards regression models will then be fitted to estimate the difference in risk of an RDT-confirmed malaria case over time of follow-up; results will be expressed as hazard ratios, and a percentage effect size will be calculated. Model diagnostics will be run to verify the proportional hazards assumption, and random effects will be modeled at the community level to account for within-cluster correlation in malaria outcomes.

Two types of models will be fitted. The first will model risk of malaria based on time to first malaria case during each child’s first continuous period of follow-up; those experiencing an RDT-confirmed malaria case will be considered dropped from the sample, whereas those lost to follow-up will be considered right-censored. The second model type will account for recurrent events—using random effects for follow-up periods nested within individual children’s data—with children experiencing a malaria case considered to be “recovered” on the day of case confirmation and will continue to contribute follow-up information after this event.

Finally, to adjust for potential confounders, covariates based on data obtained from the baseline recruitment survey will be added sequentially to each of these two models by forward stepwise selection.

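### The cRCT recruits its arms by different routes after allocation, leaving children missed by SMC delivery no stated way into the intervention sample

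*Protocol article*

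**What the plan says.** Two recruitment routes are described under Recruitment and Data Collection, Cluster Randomized Controlled Trial.

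- Control arm, both districts: "compounds will be randomly sampled by researchers using household lists from selected communities, with one eligible child recruited at random from each household".
- Intervention arm: "In the intervention arm, a researcher will follow a pair of community distributors as they administer SMC". No household list, random draw or rule for choosing the child is given for this arm.

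Children are recruited after communities are allocated. Under Sample Sizes, 76 intervention communities are chosen first. The text continues: "Then, 114 communities will be selected at random from among those remaining for inclusion in the control arm".

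Study Population defines who may receive SMC: "The study population that is eligible to receive SMC includes afebrile children". The fever rule there is tied to the day of delivery: "children with a fever on the day of SMC administration will be excluded and referred to the health facility for further evaluation". In the recruitment section, the baseline questionnaire serves "to collect individual data on each child and to confirm their eligibility".

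Covariates are collected with a view to the "association between the receipt of SP+AQ and clinically significant malaria". The Data Analysis section deals with confounding as follows: "covariates based on data obtained from the baseline recruitment survey will be added sequentially to each of these two models by forward stepwise selection". The first specific objective is the effectiveness of SMC in reducing malaria incidence among children aged 3 to 59 months.

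**The concern.** Random allocation of communities makes the communities comparable. It does not make the sampled children comparable if sampling happens afterwards and works differently in each arm. Here the control sample represents households on a list, while the intervention sample comes from contacts made during SMC delivery. A child whom the distributors do not find, or whose caregiver declines SMC, has no described way in. The same kind of child in a control community is still on the list and can be drawn.

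Two things are at stake. First, if the omitted children differ in malaria risk, the primary comparison is biased whatever the drugs do. Second, a sample of children reached by delivery does not answer the programme-effectiveness question in objective 1, because eligible children whom the programme fails to reach are part of that question.

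The fever rule adds an uncertainty. It refers to an SMC administration day, which control communities do not have. If it were not applied at control recruitment, a child already ill could enter the control arm and soon count as a case.

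**Working it through.** **1. The two routes side by side**

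| Feature | Control | Intervention |
|---|---|---|
| Frame | Household list | Contacts during SMC delivery |
| Choice of child | One at random per household | Not stated |
| Fever check at recruitment | Possible through the eligibility check; not stated | Tied to the day of SMC administration |
| Missed by delivery, or SMC declined | Remains in the frame | No stated way in |
| Absent, or no study consent | Lost | Lost |

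Only the fourth row is one-sided on the text as it stands. Stepwise covariate adjustment works on enrolled children and cannot restore those never enrolled.

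**2. The plan's own sample size (context only)**

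Inputs from Sample Sizes: risks 0.20 and 0.12, intracluster correlation 0.23, 15 children per cluster, ratio 1:1.5, 80% power, 5% level (taken as two-sided).

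- Design effect = 1 + (15 − 1) × 0.23 = 4.22.
- Pooled two-proportion formula with the smaller arm at 0.20: 270 × 4.22 = 1139.4, giving 76 and 114 clusters, or 2850 children. This matches exactly (power 80.1%).
- With the arms as labelled (1140 intervention, 1710 control), power is 78.8%.

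This point disputes no figure in the calculation. The effective sizes used below are 1140/4.22 = 270 and 1710/4.22 = 405.

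**3. What an omitted group could do if SMC had no effect**

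The document gives no omitted share f and no relative risk r for omitted children against the rest, so both are assumed. Controls represent all children at risk 0.20. The intervention sample lacks the share f.

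Intervention risk = 0.20 / (1 − f + f × r).

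| f | r | Intervention risk | Spurious risk ratio | Chance of a false significant reduction |
|---|---|---|---|---|
| 5% | 2 | 0.190 | 0.95 | 5% |
| 10% | 2 | 0.182 | 0.91 | 8% |
| 10% | 3 | 0.167 | 0.83 | 19% |
| 20% | 2 | 0.167 | 0.83 | 19% |
| 20% | 3 | 0.143 | 0.71 | 48% |

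The nominal chance in that direction is 2.5%. The last column assumes a test that allows for clustering through the design effect.

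The direction depends on r. With r = 0.5 and f = 20%, intervention risk = 0.20 / (0.80 + 0.10) = 0.222, a risk ratio of 1.11 against SMC.

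**4. The fever check, if it were applied in one arm only**

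Assume a seasonal risk of 18% in afebrile children, a share f febrile at recruitment, and a share c of those confirmed at a facility. Control risk = (1 − f) × 0.18 + f × c; intervention risk = 0.18.

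- c = 0.50: f = 5% gives 0.196 and f = 15% gives 0.228, spurious reductions of 8% and 21%.
- c = 0.25: f = 5% gives 0.1835 and f = 15% gives 0.1905, spurious reductions of 2% and 6%.
- Same check in both arms: this component disappears.

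**5. Change of estimand**

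Assume unreached children have the same baseline risk and no indirect protection. Then effect by allocation = coverage × effect in children reached. With the 33% minimum effect in Sample Sizes and an assumed coverage of 80% to 95%: 0.80 × 33% = 26% and 0.95 × 33% = 31%. This is a difference in what is estimated, not a false-positive risk.

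**The case against.** The strongest reply is that the recruitment text is short and much of the worry fills its silences.

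- A reader might infer that febrile children are removed from the intervention arm only. The document does not support that. Being afebrile is part of SMC eligibility in Study Population, control recruitment takes an eligible child, the questionnaire confirms eligibility, and Ethical Considerations admits only participants meeting the inclusion criteria. What stands is that the text does not settle whether fever is checked on the day a control child is recruited.
- A reader might infer that absent, refusing or remote families are lost from one arm only. Control children also need caregiver consent and a completed questionnaire, and researchers must reach their compounds. Only losses specific to SMC delivery are clearly one-sided. Phase 1 delivery was door to door with high reported coverage, so this group may be small.
- Calling the intervention route a convenience sample, or saying several children per household are taken, goes beyond the text. How the child is chosen there is not described, and an article may leave that to the full protocol.
- A reader might infer that the analysis is by receipt of drug. The phrase about receipt explains why covariates are collected; Data Analysis compares children by arm.
- A child referred for fever is not said to be barred for good. Later enrolment is not addressed.
- All magnitudes rest on assumed inputs. Study Setting says districts with low access to care and low treatment seeking were favoured, which points towards the lower end of the fever illustration.

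These replies narrow the point but do not remove it. Even with an identical fever check, the stated frame and its link to treatment delivery differ by arm after allocation.

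**Conclusion.** The concern holds in this form: recruitment differs by arm after allocation, and children missed by delivery or declining SMC have no stated route into the intervention sample while remaining in the control frame. Whether the fever exclusion is applied at control recruitment is unclear, and no more than that can be said.

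The consequence is a risk of selection bias in the primary comparison and a shift from programme effectiveness towards the effect in children reached. The bias probably favours SMC, on the assumption that omitted children are at higher risk, but neither size nor direction can be derived from the document. Under the assumed ranges, the omitted group alone gives risk ratios of 0.95 to 0.71 with no SMC effect, and it reverses if those children are at lower risk. A one-sided fever check would give a spurious reduction anywhere from about 2% to 21%; a check common to both arms would give none.

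**What to change.** **Design, for any recruitment still to come.** Use the same household-list draw and the same random choice of one eligible child per household in both arms, over the same calendar period. Apply the same eligibility check, fever included, at enrolment in both arms. Enrol intervention children whether or not SMC reaches them, start follow-up at enrolment, and analyse by the community's allocation. This concerns entry to the research sample only, not who is given SMC.

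Cost: household lists for the 76 intervention communities and a revised recruitment instruction. No more children are needed. The observed effect will probably be smaller, because children not reached will be counted in the intervention arm.

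**Analysis, where recruitment is complete.** The Results section says data collection concluded in mid-June 2022, so the following applies to this round:

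- Start counting cases at the same lag after enrolment in both arms, with the lag fixed before analysis. Some early cases are lost.
- As a sensitivity analysis, also exclude controls febrile at enrolment, but only if fever on that day was recorded. The only fever variable the article names covers the preceding month, which will not serve.
- Describe the estimate as the effect in children reached by SMC, not as programme effectiveness.

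None of these restores children who were never enrolled, so the limitation should be stated alongside the primary result.
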